## 10.2 Prevention and Management of Infusion-related Reactions

Subjects should be given dexamethasone 5 mg before infusion of umbilical cord-derived MSCs to prevent infusion reactions.

**Infusion-related reaction*****CTCAE Term**

| **Grade** | **CTCAE Term** |
| --- | --- |
| 1 | Mild transient reaction; infusion interruption not indicated; intervention not indicated |
| 2 | Therapy or infusion interruption indicated but responds promptly to symptomatic treatment (e.g., antihistamines, NSAIDs, narcotics, IV fluids); prophylactic medications indicated for ≤24 hrs |
| 3 | Prolonged (e.g. not rapidly responsive to symptomatic medication and/or brief interruption of infusion); recurrence of symptoms following initial improvement; hospitalization indicated for clinical sequelae |
| 4 | Life-threatening consequences; urgent intervention indicated |
| 5 | Death |

Definition: A disorder characterized by an adverse reaction to the infusion of pharmacological or biological substances.

### 10.2.1 Grade 1 or 2 Infusion-related Reactions

If subjects experience Grade 1 infusion-related reactions, there is no need to interrupt the infusion and add treatment. However, investigators can decide whether to take the same measures as for Grade 2 infusion-related reactions based on the assessment of the actual situation of the patients. If patients have Grade 2 infusion-related reactions:

- - - The infusion should be stopped immediately.
    - Subjects should receive appropriate treatment with H1 receptor antagonists and/or paracetamol or prednisolone (for Grade 1 infusion-related reactions, treatment may be assessed by the investigator on a case-by-case basis).
    - Once symptoms are relieved, the infusion can be continued at an infusion rate not exceeding 50% of the initial rate until complete dosing.

### 10.2.2 Grade 3 Infusion-related Reactions

If subjects experience a Grade 3 infusion-related reactions:

- - - The infusion should be stopped immediately.
    - Subjects should receive appropriate treatment with H1 receptor antagonists and/or paracetamol or prednisolone as clinically needed, with additional drugs added such as epinephrine and bronchodilators if needed.
    - Once symptoms are relieved, the infusion can be continued at an infusion rate not exceeding 50% of the initial rate until complete dosing. If Grade 3 symptoms recur, repeat the above steps. When the Grade 3 infusion-related reactions occur for the third time, subjects should terminate the infusion and should not receive further study drug treatment.

### 10.2.3 Grade 4 Infusion-related Reactions

If subjects experience a Grade 4 infusion-related reaction:

- - - The infusion should be stopped immediately.
    - Subjects should receive appropriate treatment with H1 receptor antagonists and/or paracetamol or prednisolone (as clinically needed), with additional drugs added (e.g., epinephrine, bronchodilators) if needed.
    - Subjects should no longer receive study drug treatment.

# Management of Concomitant Medication or Treatment, Emergency Treatment

## 11.1 Screening Period and Baseline Period (-28d--0d):

Subjects are allowed to maintain stable ITP treatment according to the Chinese ITP treatment guidelines during the screening period and baseline period of the study, including but not limited to glucocorticoids, thrombopoietin receptor agonists, azathioprine, danazol, cyclosporine A and mycophenolate mofetil, tacrolimus, retinoic acid, etc., and the dose of the above drugs should not be increased;

Among them, the dose of glucocorticoids (less than or equal to 0.5mg/kg prednisone or equivalent dose of glucocorticoids) and thrombopoietin receptor agonists should be stable for at least 4 weeks, and the dose of azathioprine, danazol, cyclosporine A, mycophenolate mofetil, tacrolimus, and retinoic acid should be stable for at least 12 weeks;

The start of other drugs for platelet elevation therapy is prohibited, including but not limited to thrombopoietin receptor agonists, rituximab, CD38 monoclonal antibody, and other clinical trial drugs, to avoid a significant impact on efficacy analysis of the umbilical cord-derived MSCs;

## 11.2 Administration Period (0d--4w):

Subjects are allowed to maintain stable ITP treatment according to the Chinese ITP treatment guidelines at the beginning of the study, including but not limited to glucocorticoids, thrombopoietin receptor agonists, azathioprine, danazol, cyclosporine A and mycophenolate mofetil, tacrolimus, retinoic acid, etc., and the dose of the above drugs should not be increased;

Among them, the dose of steroids and thrombopoietin receptor agonists should be stable for at least 4 weeks, and the dose of azathioprine, danazol, cyclosporine A, mycophenolate mofetil, tacrolimus, and retinoic acid should be stable for at least 12 weeks;

The start of other drugs for platelet elevation therapy is prohibited, including but not limited to thrombopoietin receptor agonists, rituximab, CD38 monoclonal antibody, and other clinical trial drugs, to avoid a significant impact on efficacy analysis of the umbilical cord-derived MSCs;

Concomitant ITP medications can be reduced or phased out if subjects have a platelet count ≥50×10^9^/L for at least 2 weeks according to Chinese ITP Guidelines or medical routine.

## 11.3 Follow-up Period (5w-28w):

Concomitant ITP medications can be reduced or phased out if subjects have a platelet count ≥50×10^9^/L for at least 2 weeks after completion of study therapy. Investigators can reduce the concomitant ITP medications according to Chinese ITP Guidelines or medical routine.

After completion of the study treatment, if the subject's platelet count decreases again after a significant increase, the subject's platelet count is less than 30 ×10^9^/L or bleeding symptoms occur, and the investigator judges that the treatment is effective and the case recurs, the investigator could initiate retreatment according to the Chinese ITP Guidelines or medical routine.

## 11.4 Additional Follow-up Period (> 28w):

After the end of the study, patients who have responded to MSC treatment can continue to be followed up to observe changes in platelet levels until relapse. All enrolled patients need to be followed up for a long time (> 2 years) to observe the occurrence of malignant tumors.

## 11.5 Emergency Treatment of ITP

The investigator is permitted to decide whether emergency treatment or rescue therapy for ITP is required at any time with the use of IVIG, platelet transfusion, TPORAs, glucocorticoids, etc.

Any changes in concomitant medication must be recorded in the medical record and case report form (CRF), including the name, dose of the drug, frequency of medication, start and stop dates of medication, and reasons.

# Compassionate use Regimen:

1. Applicable subjects: In this study, subjects who have no obvious adverse reactions after umbilical cord-derived MSCs infusion and respond to the treatment, if the platelet count decreases again, and is judged as relapse by the investigator, and the subjects request another infusion, umbilical cord-derived MSC infusion therapy could be given again;
2. Response (R) is defined as platelet counts ≥ 30 × 10^9^/L after MSCs treatment for at least 2 times (7 days apart), and at least doubling of the baseline count with no bleeding.
3. Relapse is defined as subjects who are judged to respond to treatment after the infusion of UC-MSCs by the investigator, and whose platelet count is found to be less than 30 × 10^9^/L again after follow-up or with bleeding.
4. The inclusion and exclusion criteria, management of infusion and concomitant medications, and emergency treatment for compassionate dosing regimen are consistent with this protocol.
5. Dose of re-infusion: the final dose used in the dose-expansion phase.
6. Infusion time: At least 16 weeks after the first infusion of UC-MSCs in this study.
7. Evaluate the efficacy and safety of umbilical cord-derived MSCs again, complete the pharmacokinetic study, detect the production of MSCs’ antibodies, and monitor the immune function;
8. Continued follow-up time: at least 16 weeks after the first dose of UC-MSC infusion in the supplemental regimen.

# Criteria for Suspension and Termination of Clinical Studies

## 13.1 Investigator-decided Withdrawal

Subject withdrawal from the trial means that the investigator decides to withdraw the case from the trial when the enrolled subject appears unsuitable to continue during the trial.

1. The number of enrolled subjects does not meet the requirements.
2. Subjects have some comorbidities, complications or special physiological changes during the trial and are not suitable to continue the trial.
3. Subjects have poor compliance during the trial.
4. Subjects have adverse events or serious adverse events during the trial and are not suitable to continue the trial.
5. Subjects die.

## 13.2 Subject’s Voluntary Withdrawal

According to the informed consent, the subject has the right to withdraw from the trial. It is also considered withdrawal although the subjects do not explicitly propose to withdraw from the trial, they no longer accept medication and testing and are lost to follow-up. The reasons for their withdrawal such as poor efficacy, intolerant of certain adverse reactions, unable to continue clinical research, economic factors, or failure to follow up without reason should be known as possible and recorded.

## 13.3 Measures of Shedding Cases

The CRF of cases withdrawn for any reason should be kept, the last test results will be considered the final results and will be used for the FAS analysis of their efficacy and adverse reaction. Those who respond to the UC-MSCs before completing the full course of infusion will not be considered as shedding cases but as response ones.

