## 3.2 Study Endpoints

- Primary endpoint:

Safety endpoint: the safety and tolerance of UC-MSCs in patients with primary ITP. The safety and tolerance of UC-MSCs will be evaluated according to the incidence and severity of adverse events and serious adverse events (according to NCI CTCAE 5.0 standard).

- Secondary endpoints:

Effectiveness endpoints:

1. Platelet counts at each visit point to evaluate the response rate.
2. Percentage of subjects with platelet counts≥50×10^9^/L and ≥100×10^9^/L at least once respectively.
3. Percentage of subjects with platelet counts ≥ 30×10^9^/L and 2-fold increase from baseline at least once.
4. The time required from the first infusion to platelet counts first ≥ 50×10^9^/L.
5. Percentage of subjects receiving emergency treatment
6. Percentage of subjects with reduced concomitant medications.
7. The longest duration of the subject's platelet counts continuously ≥ 30×10^9^/L.
8. Changes in bleeding scores (WHO bleeding scores) throughout treatment.

Pharmacokinetic endpoint:

Pharmacokinetic characteristics of UC-MSCs in patients with primary ITP, especially the concentration changes of UC-MSCs in peripheral blood.

Immunogenicity endpoint:

Incidence of UC-MSCs antibodies.

Other study endpoints:

Changes in immune status in vivo after UC-MSCs infusion.

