### 5.23. Statistical Analysis Methods

- Basic statistical methods

All statistical analyses will be conducted using SPSS 26.0 and GraphPad Prism 9.0 software, statistical analysis will be primarily descriptive. Quantitative data will be presented as median (interquartile range), and qualitative data will be presented as n (%). The differences between groups of quantitative data will be performed using student's t tests or Wilcoxon non-parametric tests. Qualitative variables will be tested with chi-square tests or Fisher's exact tests. The methods of Kaplan-Meier will be used to estimate the time-to-event data. All tests will be calculated with a two-sided significance level of 0.05.

- Safety analysis

Summary tables for adverse events have to include all AEs that occurred in the whole period of study. The correlation between treatment and AEs will be determined by the principal investigator.

- Effectiveness analysis

Proportions with 95% confidence intervals will be calculated for the efficacy endpoint.

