## 14.2 Evaluation Criteria of Efficacy

- Main efficacy criteria:

umbilical cord-derived MSCs infusion can increase the platelet count of the subjects, indicating that the drug is effective.

Evaluation criteria of efficacy:

According to the international consensus of ITP:

- complete response (CR): platelet count ≥ 100 × 10^9^ /L and no bleeding after treatment.
- response (R): platelet count ≥ 30 × 10^9^ /L and at least doubling of the baseline count, and no bleeding after treatment.
- No response (NR): platelet count <30 × 10^9^ / L or less than doubling of the baseline count or bleeding after treatment.
- Relapse: platelet count below 30 × 10^9^/L, or less than doubling of the baseline count, or bleeding, after the achievement of CR or R.

When defining a CR or R, it should be tested at least twice with an interval of at least 7 days.

- Safety efficacy criteria:

The subjects have no obvious adverse reactions caused by umbilical cord-derived MSC infusion, normal vital signs, no hepatitis B, hepatitis C, and other virus infections, and no abnormal organ function. There was no significant difference (P > 0.05) in heart, liver, and renal function between objects before and after treatment, indicating that umbilical cord-derived MSCs have no obvious side effects and are safe.

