# Quality Control and Quality Assurance

## 18.1 Quality Control

1. Determination of study protocol: The clinical study protocol is discussed and negotiated by all investigators participating in this clinical study, and is submitted to the Ethics Committee for approval after reaching a consensus on revision.
2. Control measures of laboratory quality: The manufacturers of umbilical cord MSCs have standardized testing indicators, standard operating procedures, and quality control procedures.
3. Qualification of investigators: Investigators participating in clinical research must have the professional expertise, qualifications and abilities of clinical research, pass the qualification examination. The study needs relatively fixed personnel.
4. Pre-study training: Through pre-study training, investigators can fully understand the clinical study protocol and the specific contents of each index.
5. The criteria for determining abnormalities in laboratory tests are based on the normal reference range of the test unit.
6. All observations and findings in clinical studies should be verified to ensure the data’s reliability and that the conclusions in clinical studies are derived from the original data. Ensure that there are corresponding data management measures in the clinical study and data processing stages.
7. Proactive measures should be taken for possible dropouts to control the shedding rate within 20%.
8. The investigators should ensure that the data are entered into the CRF in a correct (consistent with the actual situation of the subjects), complete (no missing items), clear (neat handwriting and easy to identify), and timely manner according to the original observation records of the subjects.

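### The last-result rule for withdrawn subjects in section 13.3 conflicts with the protocol's own definitions of response, its adverse event tables and its safety analysis set

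*Protocol*

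**What the plan says.** Protocol section 13.3 covers subjects withdrawn for whatever reason. Their case report forms are kept, and "the last test results will be considered the final results and will be used for the FAS analysis of their efficacy and adverse reaction". It then adds: "Those who respond to the UC-MSCs before completing the full course of infusion will not be considered as shedding cases but as response ones".

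Other sections of the protocol deal with the same quantities:

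- Section 14.2, on complete response (CR) and response (R): "When defining a CR or R, it should be tested at least twice with an interval of at least 7 days". Relapse is a separate category: "platelet count below 30 × 10^9^/L, or less than doubling of the baseline count, or bleeding, after the achievement of CR or R".
- Section 3.2 makes the incidence and severity of adverse events (AEs) and serious adverse events the primary endpoint. Among the secondary endpoints is "Percentage of subjects with platelet counts ≥ 30×10^9^/L and 2-fold increase from baseline at least once"; another counts subjects who reach 50 or 100 × 10^9/L at any one visit.
- Section 5.23: "Summary tables for adverse events have to include all AEs that occurred in the whole period of study".
- Section 5.22 assigns safety data to the Safety Set (treated, with at least one later safety visit) and efficacy to the Full Analysis Set, FAS (treated, with at least one efficacy evaluation).
- Section 15.2 requires subjects who withdraw because of an AE to be followed until it has fully resolved.
- Section 18.1 asks for measures to "control the shedding rate within 20" per cent.

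**The concern.** Section 13.3 is a positive rule on how withdrawn subjects enter the analysis, so it is not a detail left open for a statistical analysis plan. A plan that followed it would carry the conflict forward.

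The safety side matters more, because AE incidence is the primary endpoint. Incidence is cumulative: a subject who had an event has had it, whatever the last result shows. A rule based on the last result can lose an event that resolved earlier and can never add one.

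On efficacy, a withdrawn subject's status could rest on the last result without the confirmation that 14.2 requires of everyone. Withdrawal is also unlikely to be unrelated to outcome: 13.1 and 13.2 list AEs, death, poor efficacy and intolerance among the reasons. In a trial of about 15 subjects, one reclassified subject visibly moves a percentage. Two analysts, one following 13.3 and the other following 14.2 and 5.23, could report different rates from the same data.

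**Working it through.** **Step 1. The passages side by side.**

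| Quantity | Under 13.3 as written | Elsewhere in the protocol | Possible error |
| --- | --- | --- | --- |
| CR or R | Last results are final; early responders count as responders, with no confirmation condition repeated | 14.2: at least two tests, at least 7 days apart | Unconfirmed high last count accepted (up) |
| Response later lost | Low last result is final | 14.2: relapse after an achieved CR or R | Confirmed response overwritten (down) |
| At-least-once endpoints | Last result is final | 3.2: one qualifying count at any visit | Earlier qualifying count ignored (down) |
| AEs, which events | Last result is final | 5.23: all AEs of the whole study | Resolved event lost (down only) |
| AEs, which subjects | FAS | 5.22: Safety Set | Treated subject with a safety visit but no efficacy evaluation is left out |

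In the last row, the number of subjects counted with an AE can only fall. The percentage also depends on the smaller denominator.

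**Step 2. Number of subjects.** Section 5.21 gives 9 to 12 in escalation and 6 in expansion. 9 + 6 = 15 reproduces the minimum of 15 in section 7. The upper end is 12 + 6 = 18.

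**Step 3. Ceiling on the shift.** With the 20% limit of 18.1, the number withdrawn is m = 0.20 × N rounded down, and the largest shift is m / N.

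- N = 15: m = 3. Each subject is 1/15 = 6.7 points; maximum 3/15 = 20.0 points.
- N = 18: 0.20 × 18 = 3.6, so m = 3; maximum 3/18 = 16.7 points.
- Expansion stage, n = 6: 0.20 × 6 = 1.2, so m = 1; maximum 1/6 = 16.7 points.

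**Step 4. Illustrations.** The documents give no expected response or AE rate, so the starting counts are assumptions. Each case takes all 3 withdrawn subjects to be misclassified, with exact 95% intervals where shown.

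- Response, upward: 3/15 = 20.0% (4.3 to 48.1) becomes 6/15 = 40.0% (16.3 to 67.7). 5/15 = 33.3% (11.8 to 61.6) becomes 8/15 = 53.3% (26.6 to 78.7). 7/15 = 46.7% (21.3 to 73.4) becomes 10/15 = 66.7% (38.4 to 88.2).
- Response, downward: if three confirmed responses are overwritten, 5/15 = 33.3% becomes 2/15 = 13.3%.
- AEs: if three resolved events are lost, 5/15 = 33.3% becomes 2/15 = 13.3%, and 7/15 = 46.7% becomes 4/15 = 26.7%.

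**Step 5. What confirmation is worth.** Let q be the assumed chance that a true non-responder shows a qualifying count, with tests independent. One test is passed with probability q and two with q². The chance of at least one false responder among 3 is 1 − (1 − q)³ on one test and 1 − (1 − q²)³ on two.

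| q | One test | Two tests |
| --- | --- | --- |
| 0.1 | 27.1% | 3.0% |
| 0.2 | 48.8% | 11.5% |
| 0.3 | 65.7% | 24.6% |

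Repeated counts in one patient are probably positively correlated, which would narrow the gap between the columns.

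**The case against.** The best defence is that the sections can be read together. Section 13.3 speaks of last test results in the plural and waives nothing. Section 14.2 applies to every CR or R without exception, so 13.3 may only mean that data up to withdrawal are used and 14.2 is then applied. An AE is not naturally a test result, and 5.23, 5.22 and 15.2, with the retained case report forms, all preserve the AE count. The sentence on early responders fits 14.2, where response is an achieved state and later loss is relapse. Efficacy is secondary and mainly descriptive, with no success threshold for a shift to cross.

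Much of this stands. A reader might infer that 13.3 makes a responder of anyone with a single high count; the text does not say so. A reader might also infer that the rule inflates response among those who leave because treatment failed. The documents do not support that either: such patients would usually have a low last count and be non-responders under any rule, and a low last count can also erase a confirmed response. Nor is it established that an AE would be lost.

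The wording itself is not rescued. Section 13.3 names adverse reactions beside the last results, sends them to the FAS against 5.22, and does not say how it fits with 14.2 or 5.23. The harmless reading has to be supplied by the reader.

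**Conclusion.** The point holds as a conflict between sections, not as a demonstrated bias. Applied literally, 13.3 contradicts 14.2 and the at-least-once endpoints of 3.2 on efficacy, and 5.23 and 5.22 on safety. For AEs the error has one direction, an undercount. For response it has either.

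The 20-point ceiling rests on three assumptions: 15 subjects, withdrawals at the full 20% that 18.1 sets as a control limit rather than an expectation, and all three misclassified in the same direction. With no withdrawals the effect is nil. The ceiling also covers only cases that the protocol calls shedding. Early responders who stop are outside that count by definition, and the documents give no number for them. The point deserves correction before analysis because it touches the primary endpoint and the cohort is small.

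**What to change.** Replace the last-result rule in 13.3 with text to this effect:

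- A withdrawn subject, including one who responds before completing the infusions, is a responder only if CR or R was confirmed by two tests at least 7 days apart before withdrawal. Otherwise the subject is a non-responder in the FAS.
- The at-least-once and relapse endpoints use all observed counts, and no count is carried forward.
- All AEs up to last contact, including those recorded during AE follow-up after withdrawal, are analysed in the Safety Set. The reference to adverse reactions in the FAS is removed.

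This costs wording only: no added subjects or visits, since the flow chart already has a blood count at every visit. The reported response rate may be slightly lower and the AE rate slightly higher.
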